## Abstract

**Background:**

Mental health issues among emerging adults (aged 19-25 years) on a global scale have underscored the need to address their widespread experiences of depression and anxiety. As a result of the COVID-19 pandemic, emerging studies are being directed toward the development and deployment of digital peer emotional disclosure and support for the psychological well-being of emerging adults. However, it is important to explore the implementation and clinical effectiveness, as well as associated mechanisms of change, for optimal approaches in conducting digital peer support interventions for emerging adults’ psychological well-being.

**Objective:**

We describe a randomized controlled trial to evaluate the implementation and clinical effectiveness of Acceset, a digital peer support intervention to address emerging adult mental well-being. The intervention has 2 components. First, the digital peer support training equips befrienders (ie, peers who provide support) to harness 4 components of psychological well-being—mattering, selfhood, compassion, and mindfulness—to provide effective peer support for seekers (ie, peers who seek support). Second, Acceset incorporates psychological well-being digital markers and harnesses community engagement to drive emotional disclosure among peers.

**Methods:**

A total of 100 participants (aged 19-25 years) from the National University of Singapore will be recruited and randomized into 2 arms. In arm 1 (n=50), the seekers will use Acceset with befrienders (n=30) as well as moderators (n=30) for 3 weeks. Arm 2 comprises a wait-listed control group (n=50). A questionnaire battery will be used to monitor seekers and befrienders at 4 time points. These include baseline (before the intervention), 3 weeks (end of the intervention), and 6 and 9 weeks (carryover effect measurement). Implementation outcomes of the intervention will involve evaluation of the training curriculum with respect to adoption and fidelity as well as user acceptability of the Acceset platform and its feasibility for broader deployment. Clinical outcomes will include mattering, selfhood, compassion, mindfulness, perceived social support, and psychological well-being scores.

**Results:**

This protocol received National University of Singapore Institutional Ethics Review Board approval in October 2021. Recruitment will commence in January 2022. We expect data collection and analyses to be completed in June 2022. Preliminary findings are expected to be published in December 2022. The Cohen *d* index will be used for effect size estimation with a .05 (95% reliability) significance level and 80% power.

**Conclusions:**

This protocol considers a novel digital peer support intervention—Acceset—that incorporates components and digital markers of emerging adult mental well-being. Through the validation of the Acceset intervention, this study defines the parameters and conditions for digital peer support interventions for emerging adults.

**Trial Registration:**

ClinicalTrials.gov NCT05083676; https://clinicaltrials.gov/ct2/show/NCT05083676

**International Registered Report Identifier (IRRID):**

PRR1-10.2196/34602

## Introduction

### Background and Rationale

Emerging adulthood is a development phase that spans the ages of 19 to 25 years in most high-income economies [1]. This developmental period is marked by unique challenges as emerging adults negotiate different features such as identity exploration and feelings of instability [1]. The uncertainty that accompanies the numerous changes and the substantial fluctuations in positive and negative emotional states during this developmental period result in widespread experiences of anxiety and depressed moods [1]. The global rise in mental health issues among emerging adults has fueled concerns regarding emotional distress, including depression, anxiety, and coping mechanisms [1]. This prepandemic emotional distress has been compounded by the outbreak of COVID-19, which has brought about prolonged isolation and reduced social connections [2-4]. With the unprecedented developmental implications associated with the pandemic most directly felt by college students negotiating emerging adulthood, there is a growing need to understand how to support the mental well-being of these young individuals [5,6].

Emerging studies are showing that digital peer support may effectively address the mental well-being of young people [7,8]. Digital communication has been prevalent among emerging adults even before the pandemic [9,10] and, with the onset of the pandemic, digital peer connections have become even more pervasive and important among college students as a coping mechanism to manage emotional experiences and distress [2]. Among college students, disclosure over digital communication channels is the norm for building relational closeness [11]. The collective experiences of managing intensifying concerns and intense negative feelings associated with the onset of the pandemic has driven college students’ social connections on the web [5,6], particularly the use of digital platforms for peer emotional sharing [2]. According to the social sharing of emotions framework, emotional disclosure on the web functions as a psychological mechanism for managing emotional lability and distress, which leads to emotional regulation and recovery [12,13]. However, it is important to increase our understanding of the ideal workflow for implementing digital peer emotional disclosure and support as an intervention [7,8], how to achieve relevant clinical outcomes, and the assessment of associated mechanisms of change. Therefore, it is essential to assess the efficacy of web-based peer emotional disclosure and support systems as well as the mechanisms of change.

### Importance of Digital Peer Emotional Disclosure and Support With the Onset of the COVID-19 Pandemic

According to the social sharing of emotions framework, emotional disclosure refers to the dyadic communication of significant and personal experiences with mild to strong positive and negative emotions with one’s close social network [12-14]. It focuses on emotionally laden experiences (eg, *I was exhilarated to receive a good grade on an exam* or *I was distressed being involved in a car accident*) that are distinguished from impersonal experiences (eg, *Football games can be exciting*) and those that are mundane and void of emotional content (eg, *I went to town after school*) [12-14]. For emerging adults, peers are the primary target audience for emotional disclosure, which serves as a stress coping mechanism that facilitates emotional regulation and recovery [12-14].

With the increased prevalence of digital peer communication among emerging adults, this form of communication has the potential to facilitate and sustain relational closeness and relationship quality with friends in a scalable manner [15,16]. A possible mechanism is the social sharing of emotions as emerging adults commonly disclose their emotions through texting [17]. The importance of digital peer emotional disclosure has been heightened with the onset of the COVID-19 pandemic. The social implications of the COVID-19 pandemic, which involve uncertainty, insecurity, and a reduced sense of agency and self-directedness, have had a substantial impact on emerging adults, especially college students [18,19]. Emerging adults reported increased loneliness as social and physical distancing were implemented, and staying connected with peers through digital communication may buffer the feelings of loneliness [5,6]. For college students, their peer emotional disclosure on the web has been pivotal in managing the collective experiences of intensified concerns and intense negative feelings [2].

Emotional lability in adolescence, which stems from extensive biological and social changes in relational dynamics with parents and peers, extends into emerging adulthood as a consequence of negotiating a different set of developmental features that are new and challenging [20,21]. Studies have indicated that emerging adulthood is characterized by heightened fluctuations in emotional positivity (ie, the degree of positive emotional experiences) and negativity (ie, the degree of negative emotional experiences), which are associated with a greater propensity for anxiety and depression than in other developmental stages [1]. These normative experiences have been compounded with the onset of the pandemic. Studies have documented systematic decreases in positivity and increases in negativity that were associated with COVID-19 among adolescents and college students [2-4]. These observations demonstrate the need to prioritize the development of mental health interventions for emerging adults.

Our review of the existing literature reveals a limited understanding of how dyadic emotional disclosure and support from friends can collectively function as a digital intervention in support of the mental well-being of emerging adults [8,22-24]. Before the pandemic, the administration of digital peer support to a college student population mediated the impact of various psychological and health outcomes [25,26]. With the onset of the global pandemic, the increase in social connections on the web underscores the potential effectiveness of digital peer emotional disclosure and support to positively affect the psychological well-being of college students [2,5,6]. Digital peer support platforms may address specific areas of well-being that include anxiety, depression, and suicidal ideation [24,27]. These findings have provided the impetus for researchers, education stakeholders, and health care professionals to understand the role of peer support on digital platforms in intervening in the psychological well-being of emerging adults, particularly college students. The subsequent initiation and completion of these studies are expected to yield insights into the implementation and feasibility outcomes, user acceptability of the interventions, and clinical effectiveness in addressing anxiety and depression among college students.

### This Study

#### Overview

Research evidence indicates that interventions that successfully affect the mental well-being of emerging adults include the following elements: (1) multiple components; (2) community engagement; and (3) consultation with emerging adults on the co-design of the intervention in an effort to potentially increase adherence and sustained engagement with the platform, a critical element of scalable and effective interventions [8,28,29]. To this end, we worked with Acceset (Multimedia Appendix 1), a social enterprise that provides digital text-based intervention to harness the therapeutic potential of peer disclosure and support on the web for emerging adult mental well-being. Through Acceset, users (seekers) can anonymously share their emotional experiences and receive support from their peers (befrienders), who receive training in digital peer support skills from clinical psychologists and certified counselors (moderators). Aligned with the characteristics of successful interventions, Acceset has been designed as a digital peer support intervention that is multifaceted. It entails a digital peer support training curriculum and a digital text-based intervention, uses a community-based approach, and involves emerging adults in the design and trial process. In this study, Acceset is a stand-alone product that is used as an intervention platform.

The digital peer support training being validated in this study may serve as a comprehensive strategy built on anonymous human interaction to address mental well-being in that it harnesses 4 components of emerging adult mental well-being. Emerging literature on COVID-19 underscores the role of these components in alleviating emerging adults’ psychological distress, including anxiety and depression [30-32]. These components include (1) enhancing one’s sense of mattering (the extent to which we are important to the surrounding world and people), (2) strengthening selfhood (one’s sense of identity and role), (3) exploring compassion (the degree of sensitivity to one’s and others’ pain and distress, with a desire to alleviate that pain and distress), and (4) cultivating mindfulness (paying attention to the present moment with intention and acceptance; refer to the Methods section for details). Our consultations and pilot trial of the Acceset intervention involving emerging adults from institutes of higher learning (IHLs) revealed findings that were consistent with the literature regarding how mattering, selfhood, compassion, and mindfulness can address the mental health challenges of college students [33], particularly during the global pandemic. The coding of the content from these emerging adults’ lived experiences of mental health conditions, particularly their anxiety and depressive symptoms, revealed these 4 components that helped them manage mental health challenges (Multimedia Appendix 2). These preliminary findings provide evidence to harness the interventional potential of these 4 components in Acceset digital peer support training to build befrienders’ capacity to deliver these ingredients to provide effective peer support to seekers.

The Acceset text-based intervention (ie, the platform) incorporates digital markers of psychological well-being—specifically, emotionality (ie, positivity and negativity), motivations, and functional adjustment (ie, internalizing and externalizing behaviors)—and hinges on the peer emotional disclosure process. These are markers of psychological well-being as emerging adults’ emotional positivity and negativity, innate psychological motivations, and functional adjustment are important precedents and indicators of their well-being [1,34,35]. During the course of the digital peer interaction, when users engage with the features on the Acceset platform, they provide information about these markers, which is subsequently correlated with their self-report measures of mental well-being. These markers can shift during the course of interaction for longitudinal assessment of user mental well-being status and can potentially also stratify users toward follow-up engagement with additional mental health professionals and resources. Furthermore, the Acceset digital peer emotional disclosure and support process leverages the Singapore ecosystem and community to potentially form a web-based safety net. Designed to reduce fear and stigma, seekers (those who seek help anonymously) find help through the exchange of anonymous e-letters by disclosing the issues that bother them. By tapping on common lived experiences, the community (befrienders and moderators) relates authentically to the seeker and affirms the seeker’s emotional experiences by giving dedicated attention to the issues with which they are confronted. As a key strategy for effective engagement with digital interventions is co-designing them [8,29,30], consultations with emerging adults aged 19 to 25 years from institutes of higher education in Singapore were conducted to curate these digital features.

#### Aims, Research Questions, and Hypotheses

The Acceset intervention addresses 3 gaps in the current research. First, our published work, undertaken to identify mobile health (mHealth) platforms across popular app stores and academic databases, found 302 anxiety and depression mHealth platforms that are currently available [36]. Of note, most mHealth platforms on the market are not designed for a specific age group and, even of those used academically, only 13% are designed specifically for emerging adults. Second, despite preliminary literature that highlights the importance of digital intervention, particularly involving peer support, on emerging adults’ psychological well-being, there is a continued need to achieve effective implementation strategies and clinical outcomes [24,27]. The increasing mental health issues that stem from prolonged isolation and reduced social connections associated with the outbreak of COVID-19 further the impetus among researchers, policy makers, and other stakeholders to design effective interventions that consider the need for users to access support remotely. To this end, a digital peer support intervention provides the desirable features of remote accessibility, which enables nonstrictly in-person mental health treatment options as well as remote monitoring access.

Third, notwithstanding the benefits of harnessing the components of mattering, selfhood, compassion, and mindfulness in promoting emerging adults’ mental well-being, the proposed validation of these combined components for emerging adults’ psychological well-being represents, to the best of our knowledge, a unique prospective study. A leap forward would be to test the feasibility of incorporating these components in an mHealth platform either as a stand-alone platform or as a combination intervention. Finally, in the absence of evidence demonstrating the mechanism of change relating digital peer support interventions to emerging adults’ psychological symptoms, it is not clear whether or how digital peer support intervenes in the development of psychological symptoms or how they unfold over time. This information could potentially provide actionable knowledge for timely and relevant digital peer support interventions. To this end, this study is based on the aims and hypotheses outlined in Textbox 1.

Aims and hypotheses of this study.
**Aims and hypotheses**
Aim 1: the first aim is to evaluate the implementation effectiveness of digital peer support training between emerging adults providing support (befrienders) and emerging adults seeking help (seekers).Research question 1a: is Acceset digital peer support training an effective training curriculum in providing peer support?Hypothesis 1a: the digital peer support training is effective for befrienders in providing peer support, as demonstrated by the adoption of and fidelity to the training curriculum.Research question 1b: is the Acceset text-based intervention (ie, the platform) feasible and acceptable (ie, safe and timely) as an ongoing mechanism of support for seekers and befrienders?Hypothesis 1b: digital peer support is feasible and acceptable in offering support for emerging adults’ mental well-being, which is evidenced by 2 indicators:The engagement of the seeker-befriender-moderator interaction across the 4 time points—baseline (before the intervention), 3 weeks (conclusion of the intervention), and 6 and 9 weeks (carryover effect assessment)—that is indexed by the waiting period for seekers to receive a response. Delays are defined as a >48-hour waiting period and will be categorized based on the following reasons: (1) technical factors (eg, the befriender is not able to log into the platform to respond in time) and (2) human factors (eg, the befriender drops out from the study, and no replacement is found in time). An acceptable response time is within 48 hours, and this is emphasized during Acceset digital peer support training for befrienders [37].The use of technical features of the Acceset platform that is measured by the seeker dropout rate at each stage of engagement with the Acceset platform, the number of visits on the study registration website, the number of participants who registered with Acceset, the average number of letters exchanged, and the average number of emotion and functional adjustment stickers and motivation graphic interface formats used [37].Research question 1c: is the Acceset text-based intervention (ie, the platform) feasible and acceptable (ie, safe and timely) as an ongoing mechanism of support that identifies individuals who are at an unacceptably high risk of mental health conditions?Hypothesis 1c: digital peer support is feasible and acceptable in offering support for emerging adults’ mental well-being by identifying individuals who are at an unacceptably high risk of mental health conditions related to depression and suicidality, which is measured before and during engagement based on 3 means—specifically, the Acceset algorithm detection of the content of the letters, the moderators’ vetting of the content of seekers’ letters, and the seekers’ self-report responses to the 9-item Patient Health Questionnaire [38] (refer to the Implementation Outcomes section for details [37]).Aim 2: the second aim is to elucidate whether Acceset digital peer support harnesses the 4 components of emerging adult mental health—mattering, selfhood, compassion, and mindfulness.Research question 2a: does Acceset digital peer support enhance the 4 components among seekers and befrienders?Hypothesis 2a: Acceset digital peer support (training) increases the 4 components among befrienders (before and after training) and seekers (over the course of the study across 4 time points).Research question 2b: is Acceset digital peer support effective in improving emerging adult mental well-being?Hypothesis 2b: digital peer support leads to significantly better mental well-being of seekers compared with the control group. This effect is sustained beyond the period of the intervention.Aim 3: the third aim is to investigate the mechanism of change in emerging adult mental well-being involving digital peer support (delivered by the Acceset platform).Research question 3: what is the mechanism explaining the change in emerging adult mental well-being involving digital peer support?Hypothesis 3: the initial level and rate of change (ie, growth factors) of befrienders’ web-based support positively predict the growth factors of seekers’ psychological well-being in accordance with latent growth curve modeling.

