With regard to user referral to appropriate mental health support providers, the seeker-befriender-moderator interaction will identify participants at an unacceptably high risk of depression and suicidality before and during engagement based on 3 means. First, the Acceset algorithm will scan the content of the letter exchanges for high negativity and suicidal thoughts and expressions. Second, moderators with the required background and assessment tools will identify seekers at risk by vetting all the letter exchanges for high negativity and suicidal thoughts and expressions. Third, seekers will self-report their responses to the PHQ-9, and those that meet the clinical cutoff scores (PHQ-9 >9) will be excluded at the start of the study. During the course of the study across the 4 time points, seekers with an unacceptably high risk of depression and suicidality (PHQ-9 >9) will be referred to an appropriate mental health care provider, including counseling centers and hotlines, on the NUS campus. Seekers’ self-reported responses to the PHQ-9 serve as the primary risk assessment to make referrals to appropriate mental health support providers.

At recruitment, we will assess the percentage of participants identified as being at an unacceptably high risk of depression and suicidality meeting the clinical cutoff of PHQ-9 >9 that has a sensitivity of 88% and specificity of 88% for major depression [38] and exclude them from the study. During the course of the study, we will ascertain the percentage of events when a befriender correctly alerts the moderator that the seeker is at an unacceptably high risk of depression and suicidality as confirmed by the moderator, who will vet every letter exchange. During the course of the study and for every letter exchange, we will tabulate the percentage of events when a moderator correctly identifies a seeker with an unacceptably high risk of depression and suicidality. Both the befrienders and moderators will use the PHQ-9 as a systematized coding structure to code seekers’ letter content to ensure generalizability and validity in risk assessment across both coders—befrienders and moderators. Finally, we will tabulate the percentage of events when a seeker who is at an unacceptably high risk of depression and suicidality (both during the recruitment process and during engagement with the platform) receives directions to an appropriate mental health care provider, including counseling centers and hotlines, on the NUS campus.

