#### Clinical Outcomes

To address research question 2a and hypothesis 2a, we will examine whether the Acceset training curriculum can enhance the 4 components of psychological well-being among befrienders and seekers. We will compare the change in mattering, selfhood, compassion, and mindfulness scores of befrienders between baseline and following Acceset training (ie, before vs after training) and those of seekers over the course of the study. As for research question 2b and hypothesis 2b, we hypothesized that engagement with Acceset digital peer support will lead to improved mental well-being of the seekers compared with the control group and that this effect may be sustained beyond the period of the intervention. To assess these effects, we will evaluate the change in mental well-being of the participants in both study groups (intervention and control) after 3, 6, and 9 weeks from baseline using self-report questionnaires. Seekers will provide responses pertaining to help-seeking behavior beyond the Acceset platform at weeks 6 and 9 using the perceived social support measure in the questionnaire battery. We will assess the correlations of the 3 digital features—comprising emotion and functional adjustment stickers and motivation GIFs, which reflect seekers’ mental well-being during engagement with the platform—with their well-being scores from the questionnaires.

The scale or set of scales used to assess the clinical outcomes, including the 4 components of psychological well-being underpinning the Acceset training curriculum, measures of seekers’ well-being, and perceived social support, are outlined in the following paragraph.

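### Acceptable is defined to include safe, but the evidence assigned to hypotheses 1b and 1c would not register seekers getting worse, and the between-arm PHQ-9 data are not linked to the safety claim

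*Protocol article*

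**What the plan says.** In Textbox 1 (Aims and hypotheses), research question 1b asks whether the platform is "feasible and acceptable (ie, safe and timely) as an ongoing mechanism of support for seekers and befrienders". Research question 1c uses the same gloss for a mechanism that finds people at high risk.

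The evidence is then fixed, hypothesis by hypothesis:

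- **Hypothesis 1b:** "digital peer support is feasible and acceptable in offering support for emerging adults’ mental well-being, which is evidenced by 2 indicators". The first is engagement "that is indexed by the waiting period for seekers to receive a response", with more than 48 hours counted as a delay. The second is "The use of technical features of the Acceset platform that is measured by the seeker dropout rate at each stage of engagement", together with website visits, registrations, letters exchanged, and stickers and GIFs used.
- **Hypothesis 1c:** support is shown "by identifying individuals who are at an unacceptably high risk of mental health conditions related to depression and suicidality", through the algorithm, moderator vetting and the PHQ-9.

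Implementation Outcomes repeats these measures and says how 1c is scored. For befrienders, "we will ascertain the percentage of events when a befriender correctly alerts the moderator". For moderators, "we will tabulate the percentage of events when a moderator correctly identifies a seeker with an unacceptably high risk of depression and suicidality". It adds the percentage over the cutoff at recruitment and the percentage of high-risk seekers directed to care.

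The control arm enters under research question 2b. In Clinical Outcomes, "we will evaluate the change in mental well-being of the participants in both study groups (intervention and control) after 3, 6, and 9 weeks". The PHQ-9 and an anxiety scale are among the outcomes, and Data Collection, Management, and Analyses compares the groups by two-tailed independent-sample t tests. Eligibility Criteria does not admit seekers scoring above 9 on the PHQ-9. During the study, a score above 9 triggers referral.

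**The concern.** A safety conclusion needs a measure that looks worse when participants are harmed. Reply time and feature use describe how the service runs. The percentages correctly identified or referred describe how well the safety net catches people, not how many people need catching. A seeker who deteriorates and is noticed is a detection success whether the platform found the deterioration or contributed to it.

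The trial holds the data that could separate the two, because both arms complete the questionnaire battery. As written, though, the between-arm comparison answers only the benefit question in hypothesis 2b. A report that follows the plan could therefore call the platform safe on reply times and detection rates, without showing how often seekers crossed the cutoff in each arm.

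**Working it through.** The plan gives no figure for this point, so there is none to reproduce. The check sets each measure against one question: would it look worse if more seekers deteriorated?

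**1. The assigned measures**

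| Measure | Hypothesis | Looks worse if seekers deteriorate? |
|---|---|---|
| Reply waiting time | 1b | No |
| Letters, stickers, GIFs, visits, registrations | 1b | No clear direction |
| Seeker dropout by stage | 1b | Possibly, but read as feature use |
| Percentage correctly identified | 1c | No |
| Percentage directed to care | 1c | No |

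**2. Detection percentage.** Assume 88% of high-risk seekers are detected. This borrows the PHQ-9 sensitivity quoted for major depression and is an assumption. Of 50 arm 1 seekers:

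- 5 high-risk: 0.88 × 5 = 4.4 identified, 88%
- 10 high-risk: 0.88 × 10 = 8.8 identified, 88%
- 20 high-risk: 0.88 × 20 = 17.6 identified, 88%

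The percentage does not move while the burden quadruples. It is insensitive to harm; it does not rise with it.

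**3. Means can hide a minority.** Assume 40 of 50 seekers improve by 2 points and 10 worsen by 5. The mean change is (40 × −2 + 10 × 5)/50 = −0.6, with 10/50 = 20% worse. The SD is √(0.8 × 1.4² + 0.2 × 5.6²) = √7.84 = 2.8. Against an assumed control mean of 0 with the same SD, d = 0.6/2.8 = 0.21. With 50 per arm and two-sided 0.05, 80% power is reached at d of about 0.57, so the t test would probably show nothing in either direction.

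**4. Why arm 2 is needed.** Everyone starts at 9 or below, so each later score above 9 is a new crossing. Some will occur without any effect of the platform, and a count in arm 1 alone cannot separate these.

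**5. What 50 per arm can show.** Crossing rates are assumed. The half-width is 1.96 × √[(p₁(1−p₁) + p₂(1−p₂))/50].

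- 10% v 20%: 1.96 × √[(0.09 + 0.16)/50] = 0.139. Difference 10 points, interval about −4 to 24.
- 10% v 30%: 1.96 × √[(0.09 + 0.21)/50] = 0.152. Difference 20 points, interval about 5 to 35.
- 10% v 10%: 1.96 × √[(0.09 + 0.09)/50] = 0.118. Even with equal rates, an excess of up to about 12 points is not excluded.
- 0 of 50 in one arm: the one-sided 95% upper bound is 1 − 0.05^(1/50) = 5.8%.

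Power to detect a doubling (two-sided 0.05, pooled variance under the null; p̄ is the mean of the two rates and Δ their difference) is Φ{[Δ − 1.96√(2p̄(1−p̄)/50)] / √[(p₁(1−p₁) + p₂(1−p₂))/50]}:

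| Control rate (assumed) | Power for a doubling | Fisher exact | Per arm for 80% |
|---|---|---|---|
| 5% | 0.155 | 0.063 | 435 |
| 10% | 0.286 | 0.195 | 199 |
| 20% | 0.590 | 0.515 | 82 |

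The crossing table is therefore a description with an interval, not a test.

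**The case against.** The strongest reply is that Aim 1 is the implementation half of a hybrid design. In research question 1c, safe can be read as the working of the detection and referral system, for which detection and referral percentages are sensible. The word safe appears in the research questions and not in hypotheses 1b and 1c. The PHQ-9 and anxiety scores are compared between arms by two-tailed tests, so average worsening would count against the platform under 2b. A condensed article may leave adverse-event reporting and threshold tables to fuller documents. The proposed table would usually miss a doubling from 10% to 20%, and a move from 9 to 10 may be measurement noise.

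Much of this stands and limits the point. A reader might infer that the trial has no harm measure or makes no use of its wait-list arm. The documents do not support that: the 2b comparison uses both arms and can show mean worsening, PHQ-9 scores above 9 are monitored with referral, and seeker dropout is a 1b indicator. The absence of general adverse-event reporting from the article is not part of this point.

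What does not answer it: the hypotheses are offered as answers to research questions that contain the word safe, and the article itself names the evidence for each. That assignment is not detail left to another document. Nothing links the 2b comparison to the safety conclusion. Dropout is labelled feature use. The planned check compares completers with dropouts within each group; risk-related dropout is not compared between arms.

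**Conclusion.** The point holds in a limited form. The measures assigned to hypotheses 1b and 1c cannot support the word safe, because they would not clearly look worse if seekers deteriorated. The between-arm PHQ-9 comparison that could speak to safety is attached only to the benefit question and, as stated, is made on group means.

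A reader might go further and infer that worsened seekers would count as evidence for the platform. The documents do not support that: 1c is scored mainly as percentages correctly identified or referred, which do not rise merely because more seekers worsen.

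The consequence is a safety statement stronger than its evidence. Randomisation, data collection and the test of hypothesis 2b are unaffected. The figures rest on assumed crossing rates and an assumed 88% detection rate. A crossing of the cutoff is a marker, and a one-point crossing need not be a clinical deterioration.

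**What to change.** 1. In research questions 1b and 1c, remove safe from what waiting time, feature use and detection or referral percentages are said to show.
2. Rest any safety statement on the proportion of randomised seekers with PHQ-9 above 9 at weeks 3, 6 and 9, by arm as randomised, with the difference and its 95% CI. Use only the time points at which arm 2 is still wait-listed.
3. Report risk-related dropouts by arm beside it, since the plan expects some high-risk seekers to leave and their later scores may be missing.
4. Report detections made only from letters separately. Arm 2 writes no letters while waiting, so they have no counterpart there.
5. Present the table as estimation, and limit any conclusion to what the interval excludes. With 50 per arm, only large excesses can be excluded.
6. Label the table as added after data collection, because the Results section says collection ended in June 2022 and analysis is under way.

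The cost is one table and a wording change, with no new data or visits. The downside is a wide interval and a more modest safety statement. The table covers seekers only.
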